### Aim and objectives

This trial aims to assess whether educational outreach visits are superior to usual implementation of guidelines regarding the reduction of inappropriate prescribing. The primary outcomes will be the long-term (18 months) effects in the prescription of cyclooxygenase-2 (COX-2) inhibitors, and omeprazole, by family physicians. The secondary outcomes will be the short (1 month) and medium-term (6 months) effects of educational outreach visits in the prescription of these two drug classes. Other secondary endpoints will be the short, medium and long-term effects of educational outreach visits in the prescription of clopidogrel. Finally, the trial will determine the cost-benefit of educational outreach visits.

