### Data collection

Researchers will have access to prescription data through a data monitoring system operated by the Regional Health Administration. Data will be collected and provided by employees from this Administration according to researcher defined specifications. Importantly, researchers will not be directly involved in data collection. This information arrives with a two-month delay from the date the prescription is dispensed. The prescription information contained there can be either for acute conditions - single prescriptions with up to two packages to be dispensed within 30 days; or for chronic usage - three identical prescriptions (up to two packages each) to be dispensed within 6 months. Within the drug classes of this study, only NSAIDs cannot be prescribed for chronic usage. Adverse events cannot be collected in this study because only prescription data is available.

Detailers will record whether the planned visit was effectively accomplished, whether it had the planned duration, the number of physicians (including residents) present, whether the visit was made on patient visit time or off hours, the number of times the detailer had previously visited that physician, and feedback from the physician about the educational materials.

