We have chosen prescription-related outcomes over clinical outcomes. In Portugal, hospital discharge diagnoses (coded through the 9^th^ revision of the International Classification of Diseases) are routinely collected for hospital reimbursement purposes, but are only available after considerable delay. Primary care diagnoses (coded through the 2^nd^ edition of the International Classification of Primary Care) began to be collected in 2007 and are available in the regional database within only one month of registration in the medical record. However, both hospital and primary care diagnoses have not been validated for comprehensiveness and accuracy. Moreover, diagnoses associated with incentives may be recorded more often than those without incentives [30,31]. Hence, we have chosen to use prescription patterns as main outcomes. All prescription data in the National Health Service is gathered by the Ministry of Health for pharmacy reimbursement purposes. Data are available for both ordered and dispensed prescriptions. Pilot data from three primary care units showed that only about 60% of the prescribed drugs are actually dispensed. This likely arises from several factors: lack of patient adherence to prescriptions, the inability of physicians to match monthly amounts of different medicines in the same prescription sheet (hence the patient will not fill the entire prescription), and errors in printing and composing prescriptions that are subsequently not handed to the patient nor removed from the electronic medical record. For all these reasons, we opted to use dispensed prescriptions data as primary outcomes rather than ordered prescriptions.

Proton pump inhibitors and antiplatelets may be placed in chronic prescriptions, valid for up to six months. This means that data for these drugs may include prescriptions as old as six months prior to dispensing (and hence up to six months prior to the intervention). This may result in an underestimation of the intervention’s effect in secondary outcomes (one and six months, which may still include many lingering old prescriptions). This underestimation will be resolved for the primary outcomes (18 months) because by that time all prescriptions issued prior to the intervention will have been dispensed. However, if the intervention effect decreases over time, prescriptions issued as early as 12 months after the intervention may still be dispensed at 18 months and thus lead to an overestimation of the primary outcomes.

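### Dispensing-date timing can strongly dilute the 1-month omeprazole and clopidogrel results and, if the effect wanes, modestly overstate omeprazole at 18 months; no supporting analysis by issue date is described

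*Protocol article*

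**What the plan says.** The objective (Aim and objectives) is the effect of visits on physicians' prescribing at 18 months for the two primary outcomes, and earlier for the secondary ones: "The secondary outcomes will be the short (1 month) and medium-term (6 months) effects of educational outreach visits". Clopidogrel is a secondary outcome at 1, 6 and 18 months. Persistence over the long term is one of the questions named in the abstract.

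The data source is dispensing. Under Strengths and limitations: "we opted to use dispensed prescriptions data as primary outcomes rather than ordered prescriptions". Under Data collection: "This information arrives with a two-month delay from the date the prescription is dispensed". A chronic prescription consists of "three identical prescriptions (up to two packages each) to be dispensed within 6 months". The classes differ: "Proton pump inhibitors and antiplatelets may be placed in chronic prescriptions, valid for up to six months", whereas "Within the drug classes of this study, only NSAIDs cannot be prescribed for chronic usage".

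The limitations section draws the consequence itself. It expects possible underestimation at 1 and 6 months and considers this resolved at 18 months. For the 18-month results it adds a caution that applies only under a waning effect: "prescriptions issued as early as 12 months after the intervention may still be dispensed at 18 months and thus lead to an overestimation". It also states that "Data are available for both ordered and dispensed prescriptions", and explains why ordered data were not chosen: about 60% of prescribed drugs are dispensed, and misprinted orders stay in the record.

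**The concern.** The question is about decisions to prescribe after a visit, but the outcome month appears to be fixed by when the drug left the pharmacy. For omeprazole and clopidogrel the two can be up to six months apart. The 1-month result then contains decisions taken before the visit, and the 18-month result contains decisions taken from month 12 onwards.

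Elsewhere the protocol treats timing with care. It anchors outcomes to visit dates, and it assigns random reference months to control units because a gap of up to six months was thought too long. A lag of the same maximum length is left in place here.

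At stake is the reading of the time course. If the early value is too low and, under a waning effect, the late value is too high, the decline is hidden. The COX-2 primary outcome is not exposed to this six-month lag, although the limitations section speaks of the primary outcomes in the plural.

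**Working it through.** **The plan's own figure.** Inputs from Sample size: difference 5 points, alpha 0.025 (taken as two-sided), power 80%, cluster size 6, dropout 15%. With n = 2(2.241 + 0.842)² SD²/5² and design effect 1 + 5 × ICC:
- COX-2 (SD 7.4, ICC 0.249): 42 × 2.245 = 94.3; 94.3/0.85 gives 111.
- Omeprazole (SD 10.1, ICC 0.027): 78 × 1.135 = 88.5; 88.5/0.85 gives 105.

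The stated 110 per group is reproduced within rounding. The lag does not alter it. The omeprazole mean and SD behind it describe dispensed proportions.

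**Lag model (assumptions).** The effect depends on the issue date. Chronic items are dispensed either at 0, 2 and 4 months after issue, or evenly over 0 to 6 months. The documents give no chronic share, so 50% and 100% are shown.

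**Month 1: share of volume issued after the visit.**
- All chronic: ages 0, 2, 4 give 1/3 = 33%; even ages give 1/6 = 17%. A 5-point effect shows as about 1.7 or 0.8 points.
- Half chronic, with acute items all issued after the visit: 0.5 + 0.5/3 = 67%; 0.5 + 0.5/6 = 58%.
- If the outcome is instead the whole first month after the visit and acute items lag by 0 to 1 month, a constant effect is 8-17% visible (all chronic) or 29-33% visible (half chronic).

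**Month 6.** On the same whole-month reading, 92-100% of a constant effect is visible. With a 12-month half-life the issue-date effect is 3.64 points and the dispensed reading 3.83-4.22, so the bias is upward.

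**Month 18.** Inflation is the mean of 2^(age/half-life). The true effect is 5 × 2^(-18/half-life).

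| Half-life | True effect | Factor, all chronic | Excess in points | Factor, half chronic |
|---|---|---|---|---|
| 12 months | 1.77 | 1.13-1.20 | 0.23-0.35 | 1.06-1.10 |
| 6 months | 0.63 | 1.28-1.44 | 0.18-0.28 | 1.14-1.22 |

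Other shapes, on the whole-month reading with 50-100% chronic use:
- Constant effect: 5.0 read as 5.0.
- Growing effect: 7.43 read as 7.01-7.22.
- Linear fade to zero at 24 months: 1.35 read as 1.67-1.98.
- Linear fade to zero at 18 months: 0.14 read as 0.56-0.97.

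**Scale.** Standard error of the omeprazole difference = √(2 × 10.1² × 1.135/110) = 1.45 points, or 1.57 with 93.5 per group after dropout.

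**Apparent persistence, 12-month half-life.** The true 18-month/1-month ratio is 2^(-17/12) = 0.37. The observed ratio is 0.60-0.70 with half-chronic use and above 1 with all-chronic use. On the whole-month reading it is 1.2-5.3 with 50-100% chronic use. The 18-month/6-month ratio is 0.50 true against 0.50-0.55 observed.

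**The case against.** The limitation is disclosed, in both directions and with its condition. The late follow-up lets pre-visit prescriptions clear, and ordered data were set aside for stated reasons. The primary comparison is between arms at 18 months. The 18-month/1-month ratio is not a defined outcome, and the 18-month/6-month ratio is barely distorted for a 12-month half-life. In points, the excess at 18 months is under a quarter of a standard error for either half-life, and below one standard error even in the steepest fade tried. A supporting analysis could also sit in an analysis plan that is not shown.

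Most of this stands, and it rules out stronger readings that a reader might infer:
- That the 18-month effect is inflated outright. The documents and the arithmetic both make this depend on a waning effect.
- That early effects in general are diluted. This is large at 1 month only.
- That the 1-month results are mostly pre-visit prescriptions. With half-chronic use and timing at exactly one month, 58-67% is post-visit.
- That the primary outcome must be redefined. That would detach it from the sample-size inputs and from a reasoned choice of data source.

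The objection does not remove the dilution at 1 month, or its consequence for statements about persistence. An issue-date analysis also depends on what is requested from the Regional Health Administration, so it is a data-specification matter and cannot safely wait for the analysis stage.

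**Conclusion.** The concern holds in limited form. For omeprazole and clopidogrel, the 1-month secondary outcomes can be strongly diluted: 17-33% of volume is post-visit if all use is chronic, 58-67% if half is. At 6 months the distortion is small, and upward if the effect fades. At 18 months omeprazole is unbiased for a stable effect and understated for a growing one. It is modestly overstated for a waning one: 13-20%, or about 0.2-0.35 points, for a 12-month half-life with all-chronic use and a 5-point initial effect, and about half that with half-chronic use.

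The practical consequence is that a waning effect can look more persistent than it is when 18 months is set against 1 month, chiefly because the 1-month value is low. Nothing here shows that the primary conclusion would change. The sizes rest on the assumed chronic share, dispensing pattern, decay shape and reading of month 1, none of which the article fixes numerically.

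**What to change.** - Keep the dispensed outcome as primary, so that it stays aligned with the sample-size inputs.
- In the extraction specification to the Regional Health Administration, request the issue date of each dispensed item. Pre-specify a supporting analysis of the 1-, 6- and 18-month omeprazole and clopidogrel outcomes on dispensed items issued in the outcome month, with the same fixed dispensing window in both arms.
- If the issue date is not held, use ordered prescriptions issued in that month as the supporting analysis. State their known limits: about 60% are dispensed, and misprinted orders are included.
- Base statements on the time course or persistence of the omeprazole and clopidogrel effects on both analyses, not on the dispensing-date 1-month result alone.
- In the limitations text, say that of the two primary outcomes only omeprazole is exposed to the six-month lag.

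Cost: some extra data work, and a wait of up to six months for the supporting analysis, less with a shorter window. The sample size does not change. According to Trial status no unit had been randomised at submission, so the change is cheap at that stage.

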### Relationship to other studies and expected contribution of this trial

In 2008, a Cochrane Systematic review concluded that educational outreach visits had a small but consistent effect on improving prescribing behavior, and identified areas for further research, namely: head-to-head comparisons between different educational outreach strategies, process evaluation embedded into trials to assess which components influence the effectiveness of the intervention, inclusion of patient outcomes, measurement of costs and sustained/long term/multiple visits educational efforts [10]. Since its publication, a large number of trials of multifaceted interventions that included educational outreach visits have been published. However, it is not yet clear whether educational outreach has a sustained effect and whether the intervention is cost-effective in a broad range of healthcare systems. The current study is innovative and important internationally as it addresses both these questions. Locally, this trial may show the effectiveness and feasibility of a sustained educational outreach program. If successful, it may be the cornerstone for deploying large-scale programs within the Portuguese NHS. This may range from other types of prescription improvement (*e.g.*, much needed increase of generic market share, which in Portugal is only about half the share of Germany or the US; targeting innovative therapy for appropriate patients) to rational ordering of tests and even adequate screening practices. Ideally, governments and academic centers should be well positioned to apply our findings to a variety of educational outreach programs.

### Data sharing

All data is property of the Lisbon Regional Health Administration (Portuguese Ministry of Health). Other researchers wanting to access raw data will need to obtain authorization from this institution before data can be shared.

## Abbreviations

ATC: Anatomical therapeutic chemical classification; COX-2: Cyclooxygenase-2; ICC: Intra-cluster correlation coefficient; NHS: National Health Service [Portugal]; NSAIDs: Non-steroidal anti-inflammatory drugs; PPIs: Proton pump inhibitors; SD: Standard deviation.
